## Abstract

**Background:**

Circadian rhythm plays an important role as our internal body’s clock that synchronizes behavior and physiology according to the external 24-h light-dark cycle. Past studies have associated disrupted circadian rhythm with higher risk of miscarriages, preterm birth and low birth weights. This paper described the protocol of a prospective cohort study which aims to determine the circadian rhythm in pregnant women, identify its association with maternal factors during pregnancy, gestational weight gain, birth and infant outcomes.

**Methods:**

Ten government maternal and child health clinics in Kuala Lumpur, Malaysia will be randomly selected. Sample size of 438 first-trimester pregnant women will be followed-up until the birth of their infant. Salivary melatonin and cortisol concentration among subsample will be determined using enzyme-linked immunosorbent assay. Data on sleep quality, psychological distress and morningness/eveningness chronotype of pregnant women will be collected using validated questionnaires. Pedometer will be used to measure 5-day physical activity data. Total gestational weight gain will be determined at the end of pregnancy. Utilization of 3-day food record is to capture meal timing and nutrient intake. All measurements will be done in 2nd and 3rd trimester. Birth outcomes will be collected through clinic records and Centers for Disease Control and Prevention (CDC) Neonatal questionnaire. Infants will be followed-up at 6 and 12 months old to obtain anthropometric measurements.

**Discussion:**

There is a growing recognition of the role of maternal circadian rhythm, which entrains fetal circadian rhythms that may subsequently have long-term health consequences. The present study will identify the effect of circadian rhythm on pregnancy outcomes and infant growth in the first year of life.

## Background

Circadian rhythm is an endogenous process that has a periodicity of approximately 24 h [1]. It stimulates anticipation of regular and daily repeating events that take place at approximately the same time of day in organism, allowing the upregulation of most of the major physiological systems in mammals [2]. Circadian system in mammals is organized in a hierarchic manner in which the master (central) clock located in the suprachiasmatic nuclei (SCN) of the anterior hypothalamus govern this process [1, 3]. The SCN coordinates other central circadian oscillators including the hypothalamus and pituitary gland, which subsequently organizes the peripheral (local) clocks located in the peripheral tissues and aligns the entire circadian system to the external light/dark cycle [1, 3]. This allows organisms to coordinate endogenous and behavioral activities to the time of day, promoting internal and external synchronization.

Melatonin and cortisol are the most widely used biological phase markers to examine circadian rhythm [4, 5]. The secretions of these hormones are highly rhythmic, with melatonin exhibiting maximal level in the middle of night and gradual decline towards dawn while cortisol peaks in the second half of the night toward early morning, and declines to half of the peak value in the afternoon [6, 7]. Both melatonin and cortisol play a role in synchronizing the circadian rhythms in peripheral tissues to the 24-h pattern and likely provide feedback to the SCN [8].

Many emerging studies addressed the recognition of the importance of maternal circadian rhythm on pregnancy and fetal development. Throughout gestation, the fetus is inevitably exposed to maternal rhythms such as body temperature, food intake and melatonin level [9]. Entrained 24-h rhythms of fetal heart rate, movements and hormones were reported in human, non-human primates and sheep, suggesting that maternal circadian signals may contribute to the entrainment of the peripheral clock in fetus [9]. A study by Seron-ferre and his co-researchers proposed that fetal SCN and fetal organs are peripheral maternal circadian oscillators, which are entrained by maternal signals [9]. This results in internal temporal order during fetal growth, which subsequently allows for postnatal integration of the scattered fetal peripheral circadian clocks into an adult-like circadian system [9].

With the growing evidences that demonstrate the long-term impact of pregnancy environment on the development of fetus and the role of circadian system in governing physiological process and metabolic balance, identifying factors associated with circadian rhythm and its relation to pregnancy and infant growth is imperative. Understanding the circadian factors associated with pregnancy has practical importance for preventive care in ensuring a successful pregnancy and optimal development of the fetus, which is essential to lower the risk of developing postnatal diseases of an individual in later life. Therefore, this study intended to fill current research gaps by investigating the association between maternal circadian rhythm with total gestational weight gain, birth and infant outcomes, as well as determining the lifestyle factors affecting maternal circadian rhythm during pregnancy.

## Methods/design

### Study aims

The aim of the study is to determine the association of stress, physical activity and chrononutrition with circadian rhythm among pregnant women and its impact on total gestational weight gain, birth and infant outcomes. To achieve the aim, the specific research objectives to be investigated in the study are:
To determine the circadian rhythm of pregnant women in Kuala Lumpur, Malaysia.To determine the association of stress, physical activity and chrononutrition (energy and nutrient intake, energy and nutrient distribution, meal frequency, eating window, breakfast-skipping, late-night eating and intermittent fasting) with circadian rhythm among pregnant women.To determine the association of irregular circadian rhythm with total gestational weight gain, birth outcomes (birth weight, gestational age at birth and delivery method) and infant outcomes (infant weight, body composition and temperament).

The hypothesis is that mothers with irregular circadian rhythm during pregnancy are associated with higher risk of poor birth outcomes and have unfavorable outcomes, especially on the infant growth and temperament in later life.

### Study design

This prospective cohort study will approach pregnant women from their pregnancy at second and third trimester up to delivery and their infants will be followed up at the age of 6 and 12 months old respectively. The whole study is divided into two phases. Phase I (follow-up of pregnant women) will be conducted from 2019 to 2020. Data collection will be conducted during the second (gestational week 13 to 27) and third (gestational week 28 to 40) trimester of pregnancy, and upon delivery of the infant. Circadian rhythm of the pregnant women will be assessed using validated questionnaires based on their sleep quality and disturbances, stress, physical activity and chrononutrition. Pre-pregnancy BMI of the pregnant women will be obtained from all participating clinics record. Gestational weight gain of the pregnant women will be monitored throughout the gestation while information on birth outcome will be collected upon delivery. Phase II (follow-up of infant) will be conducted from 2020 to 2021 whereby infants will be followed-up at 6 and 12 months of age to obtain anthropometric measurements. Fig. 1 depicts the flow diagram of the study.

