### Exposures measures

#### Circadian rhythm

Circadian rhythm of pregnant women will be assessed using both subjective and objective measurements during second and third trimester of pregnancy. Subjective measurement of chronotype (morning and evening types) will be collected using Morningness-Eveningness questionnaire (MEQ) while objective measurement of circadian rhythm will be determined from salivary melatonin and cortisol rhythm of pregnant women. Chronotype refers to the expression of circadian rhythmicity that may vary among individuals [14]. It was demonstrated in past studies that different chronotypes exhibit vary circadian rhythms of several physiological variables [14]. Besides, sleep parameters are useful as phase markers of the circadian rhythm as well, given that sleep/wake cycle is an important aspect of circadian rhythm [5]. In this study, sleep disturbances and quality of pregnant women during second and third trimester will be determined using Pittsburgh Sleep Quality Index (PSQI) Questionnaire.

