##### Salivary melatonin and cortisol rhythm

In the present study, melatonin and cortisol will be measured using saliva samples. Both melatonin and cortisol can be measured in saliva in their free form [7]. Salivary concentrations have been shown to give an accurate indication of free or biologically active melatonin and cortisol as compared to human serum [5, 18]. Measuring salivary melatonin and cortisol can be used to characterize production patterns over each 24-h study period to facilitate comparisons between individual. Moreover, saliva is preferable to serum as a non-invasive alternative to determine melatonin and cortisol level. The taking of blood can cause variation in salivary cortisol level due to the effect of stress [7, 19].

Passive drool method will be used whereby subjects need to tilt their head forward and drooled through a funnel into a centrifuge tube [20]. Saliva sample collection will be taken at 2 time points during pregnancy, at second and third trimester respectively. The first sampling process will start at awakening in all cases, followed by 9:00, 15:00, 21:00 and 03:00 taken at 6 hourly intervals over the 24-h period. This will be done by subjects themselves and each subject will receive individual education regarding the collection process prior to the start of the data collection. To avoid saliva sample contamination with food, subjects are advised to refrain from eating a major meal or brushing their teeth with toothpaste within 30 min of sample collection [21, 22]. No chocolate or bananas, alcohol, caffeine, nicotine or drinks with artificial colorants should have been taken within the prior 12 h and on the day of sampling [21–23].

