#### Birth outcomes

Birth outcomes such as birth weight, gestational age at birth, delivery method, duration of labor, instrument-assisted labor and other information about the experience during labor will be collected from clinic record. Data on low birth weight, preterm birth and intrauterine growth restriction (IUGR) will be identified through clinic records. Preterm birth is defined as a gestational age less than 37 weeks which may contribute to low birth weight with birth weight less than 2500 g [50]. IUGR refers to a condition in which the rate of fetal growth is below normal in light of the growth potential of a specific infant as per the race and gender of the fetus [51]. An infant with IUGR is defined as being below the 10% percentile of the recommended gender-specific birthweight for gestational age according to William’s curve [52, 53]. Focus on the birth outcome will be limited to the 3 major adverse birth outcomes: low birth weight, preterm birth, and intrauterine growth restriction (IUGR). These adverse birth outcomes are the leading causes of perinatal morbidity, mortality, neurodevelopmental impairments and disabilities among newborn babies [53].

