To further examine the association between the circadian variables with total gestational weight gain, birth outcomes (birth weight, gestational age at birth), infant outcomes (weight, body composition and infant temperament scores), multiple linear regression will be used, with covariates such as maternal age and pre-pregnancy BMI. Odds ratios and 95% confidence intervals will be used to determine the strength and precision of each association after adjusting for potential confounders.

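### The third-trimester circadian assessment may fall anywhere in weeks 28 to 40, so birth-outcome models that use it lose early deliveries selectively

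*Protocol article*

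**What the plan says.** **Window.** Protocol article, Study design: "Data collection will be conducted during the second (gestational week 13 to 27) and third (gestational week 28 to 40) trimester of pregnancy". No section names a target week inside the third trimester.

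**Exposure.** Under Circadian rhythm: "Circadian rhythm of pregnant women will be assessed using both subjective and objective measurements during second and third trimester of pregnancy". For saliva: "Saliva sample collection will be taken at 2 time points during pregnancy, at second and third trimester respectively". Table 1 marks the chronotype questionnaire, the sleep index, social jetlag and the saliva sample in both trimesters.

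**Outcome.** Under Birth outcomes: "Preterm birth is defined as a gestational age less than 37 weeks". That section names preterm birth as one of three adverse birth outcomes on which the study will focus, with low birth weight and growth restriction. Outcomes measures lists birth outcomes among the main outcomes.

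**Model.** Statistical analysis relates the circadian variables to several outcomes: "birth outcomes (birth weight, gestational age at birth), infant outcomes (weight, body composition and infant temperament scores), multiple linear regression will be used". Maternal age and pre-pregnancy BMI are given as example covariates; gestational week at measurement is not named. The section does not state whether the second-trimester value, the third-trimester value or both are used. It does plan a paired comparison of circadian variables between the two trimesters.

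**The concern.** The window for the third-trimester exposure extends beyond the 37-week line that defines one of the outcomes. Two things follow for any birth-outcome model that uses third-trimester values.

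- A woman who delivers before her assessment has no third-trimester value and drops out of that model. The earlier the delivery, the likelier this is, so preterm cases (and the low birth weights that go with them) are lost preferentially.
- A woman assessed at 37 weeks or later is already past the preterm threshold, so she carries no information on preterm risk.

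The first cost is events, in a study where adverse births are the minority outcome. There is also a possible bias. Women who deliver early can only have been measured early. If circadian values change with advancing gestation, the measured value is then tied to gestational age at birth through the timing of the visit, even with no true association.

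**Working it through.** The article gives no figure for this point, so there is nothing to reproduce. The logic comes from its definitions; the sizes need assumptions, which are marked.

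**Inputs from the article.** Window: weeks 28 to 40, a width of 12 weeks (Study design). Preterm: birth before 37 weeks (Birth outcomes). Visit week: not stated.

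**1. Part of the window with no preterm risk.** A woman assessed at 37 weeks or later is still pregnant at 37 weeks, so her preterm risk is 0 by definition. That part is (40 − 37)/12 = 3/12 = 25% of the window, or 4/13 = 31% if weeks 37 to 40 are counted as whole weeks out of 13.

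**2. Loss by week of birth, even spread of visits (assumption).** For a birth at week b, P(not yet measured) = 1 − (b − 28)/12.

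| Birth week b | Calculation | Share without a third-trimester value |
|---|---|---|
| 34 | 1 − 6/12 | 50% |
| 35 | 1 − 7/12 | 42% |
| 36 | 1 − 8/12 | 33% |
| 40 | 1 − 12/12 | 0% |

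**3. The other end of the range.** If all visits fall in weeks 28 to 30 (assumption), every woman who delivers at 34, 35 or 36 weeks has already been measured. The loss for these births is 0%.

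**4. Loss over all births (simulation, illustrative).** Assumptions: planned visit uniform on 28 to 40; preterm rate 6%, 10% or 15%; preterm gestational age 37 minus an exponential with mean 2 weeks, floor 28; term gestational age normal, mean 39.3, SD 1.2, limits 37 to 42; 2,000,000 women per scenario.

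- Without a third-trimester value: about 41–42% of preterm women, about 7% of term women.
- Preterm rate among measured women: 3.9% instead of 6%, 6.5% instead of 10%, 10.1% instead of 15%.
- With visits uniform on weeks 28 to 32 instead: about 3.5% of preterm women and 0% of term women.

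**5. Possible bias through visit timing.** In the same simulation, mean measurement week is 31.8 in measured preterm women and 33.6 in measured term women, a gap of 1.8 weeks. With no true effect, an exposure drifting by d SD per week gives a false term–preterm difference of about 1.8 × d:

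- d = 0.05: 1.8 × 0.05 = 0.09 SD
- d = 0.10: 1.8 × 0.10 = 0.18 SD
- d = 0: no difference

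The drift values are assumptions; the article gives none. With visits at 28 to 32 weeks, the mean measurement weeks are equal (30.0 and 30.0), so this route closes.

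**The case against.** - **The article does not commit to third-trimester values in the birth models.** This stands. A reader might infer that birth outcomes will be regressed on both trimesters' values, but the Statistical analysis section names no trimester. The problem is conditional on that choice, and a model using only second-trimester values avoids it. The article does not say that this is the model.
- **The weeks may only define the trimesters.** Target weeks may be in the full protocol, and the flowchart is not shown. This is fair and leaves the size unknown. As written, though, any week from 28 to 40 is allowed. An analysis plan cannot recover a measurement that was never taken before an early delivery.
- **Exposure always precedes birth.** Correct. All circadian measurements are made during pregnancy, so a reader who infers that exposure and outcome are unordered would be wrong.
- **This is not immortal time bias.** Also correct. No woman is classed as exposed because she remained pregnant until a visit. The accurate terms are left truncation and selective missingness.
- **Loss alone need not bias the association.** Correct. Bias needs drift with gestational week, or visit timing or missingness related to exposure. The planned trimester comparison treats change as possible; it does not show that it occurs.
- **The covariates are examples.** True, so week at measurement is not ruled out. It is simply not named.

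**Conclusion.** The point holds in conditional form. The stated window runs past the outcome threshold, so any birth-outcome model using third-trimester values loses early deliveries preferentially and includes women who can no longer be preterm. That much follows from the article's own definitions.

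The size is not known from the documents. For births at 34 to 36 weeks the loss ranges from about zero (visits at weeks 28 to 30) to between a third and a half (visits spread evenly). It would be tempting to state the upper figure as the expected loss, or to put a number on the preterm births lost. The documents support neither, because they give no visit distribution and no preterm rate. The lost women also keep their second-trimester values.

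The main cost is events and precision. Bias is possible, not demonstrated: about 0.09 to 0.18 SD under the assumed drifts of 0.05 to 0.10 SD per week with evenly spread visits, and none from this route without drift. The changes that remove most of the problem cost little, so they are worth making.

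**What to change.** 1. Name the second-trimester measurement as the main exposure for preterm birth, gestational age at birth and birth weight. Its window closes at week 27, before the third-trimester window opens.
2. Keep third-trimester values for these outcomes as a secondary analysis, described as applying to women still pregnant at the visit. State how many women delivered before being assessed.
3. Include gestational week at measurement as a covariate in both analyses. The second-trimester window (weeks 13 to 27) is wide too.
4. Schedule the remaining third-trimester research assessments early in the existing window. The article describes recruitment as ongoing, so this can still help.

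**Cost.** Wording in the analysis section, one recorded covariate, and scheduling within the window already planned. The scientific price is that the main birth-outcome analysis does not address late-pregnancy exposure; that question moves to the secondary analysis.

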**Fig. 1 Fig1:**
[figure not shown]
Flowchart of study design

### Subject recruitment

Recruitment of subjects will commence upon obtaining approval from the respective clinics. Purposive sampling method will be used to recruit subjects in their first trimester who fulfil the following inclusion and exclusion criteria, and those who give their consent to participate. Pregnant women who attend the clinics for their routine antenatal care at 1–12 weeks will be approached and invited to participate in this study. The study objectives and procedures will be explained to the subjects and the written consent form will be signed. Information sheet will be provided for their better understanding of the study. Subjects will be asked to sign a written informed consent if they agree to participate in the study on the spot. Additional written consents will be collected from subsample of pregnant women who agree to contribute their saliva samples for circadian melatonin and cortisol rhythm analysis. Sufficient time will be given for subjects to consider their participation in the study and they may contact the research assistant should they agree to participate. Recruitment of subjects began in June 2019 and is currently on-going. To minimize loss to follow-up, efforts will be made to maintain personalised contact with the subjects and incentives will be provided.

### Inclusion and exclusion criteria

Eligible subjects must meet all the following inclusion criteria:
Malaysian women aged 19–39 years old.Able to read, write and understand English/Malay language.Singleton pregnancy.Nulliparous.

Subjects meeting any of the following criteria will be excluded from participation in the study:
Develop any co-morbidities during the study period.Handicap.Use of recreational drugs/cigarette smoking.Having medication that is known to affect sleep and melatonin or cortisol secretion.Shift workers.Transmeridian travel for the prior 3 months.Pre-existing diabetes mellitus, hypertension and anemia prior to pregnancy.

### Sample size calculation

Sample size was calculated using a formula for cohort study with two proportions. Based on the probability of low birth weight among pregnant women with irregular circadian rhythm (p1 = 0.0388) and probability of low birth weight among pregnant women with regular circadian rhythm (p2 = 0.0313), with 95% power and 5% significance level, a total of 365 of subjects are required for the study [12]. To compensate non-compliance and non-response among subjects including loss of follow up, the sample size is increased (+ 20%) to 438 pregnant women.

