### Subsample size calculation

Given the resource constraints, only a subsample will be studied for the analysis of circadian melatonin and cortisol rhythm from saliva samples. Subsample size is calculated using G*Power software, with expected effect size of 0.82, type I error rate of 0.05 and a desired power of 0.95 [13]. The total subsample size is 80 as calculated using G*Power software. To compensate for non-compliance and non-response among pregnant women, the subsample size is increased (+ 20%) to 100.

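### The stated 365 women do not follow from the stated inputs, which need about 31,250; power for the planned low-birth-weight difference is about 6–7%, not 95%

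*Protocol article*

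**What the plan says.** The section on sample size calculation in the protocol article names its method: "Sample size was calculated using a formula for cohort study with two proportions". The inputs are the "probability of low birth weight among pregnant women with irregular circadian rhythm (p1 = 0.0388") and the "probability of low birth weight among pregnant women with regular circadian rhythm (p2 = 0.0313"). The result is given as "with 95% power and 5% significance level, a total of 365 of subjects are required for the study". To cover non-compliance, non-response and loss to follow-up, "the sample size is increased (+ 20%) to 438 pregnant women". The abstract repeats the final figure: "Sample size of 438 first-trimester pregnant women will be followed-up until the birth of their infant".

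The section does not say whether the test is one- or two-sided, or what ratio of irregular to regular women was assumed. It gives no other effect size for the 365.

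The saliva subsample has its own calculation (effect size 0.82, type I error 0.05, power 0.95), which gives 80 women, and "the subsample size is increased (+ 20%) to 100".

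**The concern.** The two risks differ by 0.75 percentage points, a risk ratio of 0.0388/0.0313 = 1.24, for an outcome that affects roughly 3–4% of births. A difference that small in an outcome that uncommon needs a very large cohort, so a few hundred women at 95% power cannot be right on its face.

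This is the only justification given for the size of the main cohort. Low birth weight is one of the three adverse birth outcomes on which the article says it will focus, and birth outcomes are among the main outcomes. A reader who accepts 95% power would take a null low-birth-weight result as good evidence that irregular rhythm does not matter. If the power is close to the significance level, that result carries almost no information.

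**Working it through.** **Inputs from the sample size section.** p1 = 0.0388, p2 = 0.0313, difference d = 0.0075, alpha = 0.05, power = 0.95.

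**Assumptions, because the section is silent.** Two-sided test and equal groups. Both are varied below.

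**Step 1: try to reproduce 365.** With mean risk p̄ = (0.0388 + 0.0313)/2 = 0.03505, the pooled two-proportion formula is

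n per group = [1.960·√(2p̄(1−p̄)) + 1.645·√(p1(1−p1) + p2(1−p2))]² / d²

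- 2p̄(1−p̄) = 0.06764, square root 0.2601
- p1(1−p1) + p2(1−p2) = 0.06761, square root 0.2600
- n = [1.960 × 0.2601 + 1.645 × 0.2600]² / 0.0075² = 15,624 per group, or 31,248 in total

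The stated 365 is not reproduced; 31,248/365 is about 86.

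**Step 2: does another choice rescue it?**

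| Variant | Total women |
|---|---|
| Two-sided, 95% power, continuity correction | 31,780 |
| Two-sided, 95% power, unpooled variance | 31,240 |
| Two-sided, 95% power, arcsine | about 31,166 |
| One-sided, 95% power | 26,024 |
| Two-sided, 90% power | 25,268 |
| Two-sided, 80% power | 18,876 |
| One-sided, 80% power | 14,868 |
| Two-sided, 95% power, 2:1 split | about 35,000 |
| Two-sided, 95% power, 4:1 split | about 48,500–49,000 |

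None is near 365. Moving both decimal points (0.388 against 0.313) gives 1,049 per group, which does not match either.

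**Step 3: power with 365 women, equal groups (182.5 each).**

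- Expected low-birth-weight infants: 182.5 × 0.0388 = 7.1 against 182.5 × 0.0313 = 5.7.
- Standard error of the difference: √(0.06764/182.5) = 0.01925, more than twice d.
- Expected direction: Φ[(0.0075 − 1.960 × 0.01925)/0.01925] = Φ(−1.57) = 5.8%.
- Opposite direction: Φ(−2.35) = 0.9%. Both tails together: 6.8%.
- Exact enumeration of the two-sided chi-square test at 182 against 183 women: 6.4%.

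Other readings:

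- One-sided: 10.5%.
- All 438 women retained, two-sided: 6.3–7.1%.
- 365 per group (730 in total), two-sided: 7.9–8.5%.
- Splits between 1:4 and 4:1, two-sided: about 4–8%.

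**Step 4: what 365 women could detect for low birth weight.** Holding p2 at 3.13% with equal groups, p1 must reach about 10.5% for 80% power (risk ratio 3.4) or about 13.5% for 95% power (risk ratio 4.3).

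**Step 5: what the sample delivers for a continuous outcome such as birth weight.** For two equal groups and N women in total, the detectable difference in SD units is (1.960 + z_power)·√(4/N), with z = 0.842 for 80% and 1.645 for 95% power.

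| Analysis set | 80% power | 95% power |
|---|---|---|
| N = 365 (questionnaire exposures) | 0.29 SD | 0.38 SD |
| N = 80 (saliva-derived variables) | 0.63 SD | 0.81 SD |

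The last entry is close to the effect size of 0.82 stated for the subsample, so the figure of 80 is consistent with a two-group comparison of means, unlike the 365.

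**Step 6: the loss allowances.** 365 × 1.2 = 438, as stated; it covers a loss of 73/438 = 16.7%. For the subsample, 80 × 1.2 = 96, whereas 100 = 80/0.8. The same + 20% label therefore covers two different operations.

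**The case against.** The test's sidedness and the group ratio are unstated, so 31,250 and 6–7% are conditional figures. That is correct, but the conclusion survives every variant tried: the smallest requirement at the stated 95% power is about 26,000. The citation beside the 365 may be the source of the two risks, but it cannot change what those risks imply.

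Low birth weight is also not singled out as the one primary test. Birth and infant outcomes are listed together as main outcomes, and the statistical analysis section plans linear regression of birth weight. This stands. It confines the harm to the low-birth-weight comparison and to the justification of the cohort size; it does not make the whole study uninformative.

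Four stronger readings are tempting and should be resisted:

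- A reader might infer how the error arose, because 1.96² × 0.388 × 0.612/0.05² = 364.9. That is a single-proportion precision formula with a shifted decimal and a 5-point margin that the article never mentions. The match may be chance, and the source of 365 cannot be recovered from the document.
- A reader might infer that any unequal split lowers the power further. The total needed for 95% power does rise with marked imbalance. At 365 women, however, power counting both tails is 7.7% when 25% are irregular, against 6.8% at 1:1; it is 5.1% when 75% are irregular.
- A reader might call 438 an arithmetic error. It is not: the text says 20% was added, and 20% was added. It does not claim that 438 withstands a 20% loss.
- A reader might take 0.29 SD as the new detectable effect for circadian rhythm in general. Melatonin and cortisol variables exist only for the saliva subsample, and chronotype is analysed in three categories, not two equal groups.

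**Conclusion.** The sample size statement is wrong as written and must be corrected. The article's own inputs require a cohort about 86 times larger than stated, and the cohort it plans has power for the stated difference only slightly above the 5% false-positive rate. The base figures rest on a two-sided test and equal groups, but no choice of sidedness, allocation or formula brings the requirement near 365. The SD figures rest on a further illustrative assumption of two equal groups. The + 20% wording for the subsample is a harmless mismatch that errs upward by four women and carries no weight in this conclusion.

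**What to change.** Rewrite the sample size paragraph as follows.

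1. Keep enrolment at 438 and withdraw the claim of 95% power for low birth weight. Recruitment is under way, and some 31,000 women is not a realistic alternative.
2. State that the low-birth-weight comparison is descriptive, to be reported with its confidence interval, and that a null result is not evidence of no association. The Step 4 limits (10.5% and 13.5%) can be given as context.
3. State what the sample delivers separately for the two analysis sets, using the Step 5 figures for questionnaire-based exposures in 365 women and for saliva-derived variables in 80. Label the two-equal-groups assumption as illustrative and say that the figures were worked out after recruitment began.
4. State the test's sidedness and the assumed group ratio wherever a power figure remains.
5. Align the wording on losses: 438 is 365 plus 20% and covers 16.7% loss; 100 is 80/0.8 and covers 20%.

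The cost is one reworded paragraph and a wording correction in the next. No extra women, visits or assays are needed. The price is a less favourable power statement.
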